**Fig. 1 Fig1:**
[figure not shown]
Trial process diagram

Eligibility for the study will be confirmed if the elective surgical patient screens positively for increasing risk drinking (AUDIT C score ≥ 5) or reports at least weekly drinking of 6 or more units in one session (as judged by question 3 on AUDIT C). The trial will be discussed with eligible patients and those that express an interest in participating will be provided with a copy of the participant information sheet. They will also be asked for permission for the study team to contact them to discuss the study further and their preferred method of contact. Expressions of interest, contact information and preferred method of contact will be recorded in writing by the HCP on the expression of interest form. The patient will then be allowed time to consider their involvement in the study (minimum 24 h). After this time, the site will contact the patient to confirm positive expression of ongoing interest. If the patient confirms they are still interested, the pre-assessment clinic will be informed of the patient’s likely participation to facilitate waiting list and preoperative assessment clinic coordination for the patient’s visit. Patients scoring AUDIT C < 5 will receive positive feedback on their low-risk drinking status.

At the preoperative assessment clinic, a member of the research team (not involved in screening or delivering the intervention) will initially see the patient. The researcher will check whether the patient is still interested in participating in the study, and if so, the patient will be asked to sign the informed consent form. Once consent has been obtained, the researcher will access the Newcastle Clinical Trials Unit (NCTU) secure web-based randomisation system where they will enter the patient’s initials and date of birth. The randomisation system will then allocate the patient to either the behavioural intervention or treatment as usual groups on a 1:1 basis. Allocations are built into the randomisation system as part of study setup, and users accessing the system to randomise have no control over the allocation. This trial is not blinded.

### Intervention

The brief behavioural intervention will be delivered over two sessions—the first session which will take place in the clinic will last approximately 30 min and will be delivered following pre-assessment in the pre-assessment clinic. The second session, an optional booster session, will be delivered over the phone or in the clinic dependent on patient preference and will last approximately 20 min. This will be delivered approximately 1 week before surgery.

Following preoperative assessment, the patient and HCP will complete the baseline assessments shown in Table 3 (full 10-item AUDIT [34], EQ-5D [44, 45], Western Ontario and McMaster Universities Osteoarthritis Index (WOMAC) [46]); the HCP will then deliver the first intervention session. This session will provide participants with 5 min of simple, structured advice regarding alcohol consumption including specific feedback on risk, normative comparison, the benefits of reducing alcohol intake, strategies that could be used to reduce drinking and a personal target for reduced drinking (set by the patient). This component of the intervention specifically targets motivation. This will be followed by 15–25 min of behaviour change intervention targeting alcohol reduction and cessation and specifically focuses on volition. Intervention materials incorporate specific behaviour change techniques that target intention formation and enactment of behaviour change (e.g. information on health consequences, social support, goal setting behaviour, problem solving, restructuring the physical environment). HCPs are trained to use these techniques to tailor the intervention to the needs and preferences of the individual patient, for example, providing information relevant to and requested by the patient and supporting them to set meaningful and realistic goals that fit in with their own specific circumstances. Use of brief motivational techniques by HCPs allows them to determine the level of motivation to change and tailor the intervention to target motivation or volition at the appropriate times. Three intervention tools will be utilised:The Brief Advice (BA) tool will act as a visual aid for communicating information and will provide participating HCPs with prompts on how to structure and deliver this advice to participating patients.The Brief Behaviour Change intervention (BI) tool will be used by HCPs to guide discussion, goal setting and problem solving with participating patients and to record aspects of the intervention (e.g. goals and plans) to prompt behaviour outside of the clinical setting.The Patient Information Leaflet, based on the based on the Department of Health’s ‘Drinking and you: How much is too much?’ booklet [47], will be introduced and given to patients at the end of the intervention session along with copies of the BA and BI.

**Table 3 Tab3:** Schedule of enrolment, interventions and assessments

Time point	Study period						
	Screening	Visit 1 6–8 weeks pre-surgery	Visit 2 1–2 weeks pre-surgery (intervention arm only)	Visit 3 1 and 3 days pre-surgery	Visit 4 Up to 5 days post-surgery	Visit 5 6 weeks post-surgery	Visit 6 6 months post intervention
Enrolment:							
AUDIT C	X						
Expression of Interest	X						
Consent		X					
Randomisation		X					
Interventions:							
Intervention		X					
Booster			X				
TAU		X					
Assessments:							
AUDIT Baseline		X					
EQ-5D Baseline		X					
AUDIT Outcome			X	X		X	X
EQ-5D Outcome						X	X
WOMAC		X			X		
POMS					X		
Clavien-Dindo					X		
Interview							X

The BA and BI tools were based on the ‘How much is too much?’ Simple Structured Advice, and Extended Brief Intervention tools originally produced as part of the World Health Organization collaborative study on alcohol screening and brief intervention [48], before being adapted for use in the UK [49] and updated [37].

Patients who consent to be contacted for the second ‘booster’ session will be contacted approximately 1 week before surgery to arrange receipt. This will take place either over the telephone or in clinic at the patient’s preference. The HCP delivering the booster session will complete the full AUDIT questionnaire with patients and will aim to review or revise behavioural goals, provide feedback on performance and discuss self-monitoring to increase self-efficacy. The aim of the booster is to reinforce behaviour change by providing an opportunity for participants who had not set a goal or made a plan to reduce their drinking in the initial session the opportunity to do so. For those participants who had set a goal, the booster offers an opportunity to reflect on their experiences since the initial session, receive feedback on their progress and revise or amend their goal if necessary. Such sessions have previously been employed to address limitations presented by busy clinical settings where clinician time may be restricted and participants attention may be elsewhere (such as on their medical care) [50]; however, as booster sessions are not often well attended [51] and findings regarding the added benefit of booster sessions are mixed [52, 53], it was decided that these sessions would be optional rather than required.

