### Participants—healthcare professionals

Across the three sites, HCPs employed in the preoperative assessment clinics will receive training on study procedures, screening patients using the AUDIT C tool and completion of study baseline measures. In addition, a subset of HCPs (minimum two per centre) will be trained to deliver the brief behavioural intervention.

The intervention is detailed in Table 2. The content of the intervention materials have been defined in terms of specific behaviour change techniques (BCTs) that are the ‘active ingredients’ of the brief behavioural intervention. Group training sessions, delivered by the research associate (EL) and a health psychologist (LA), will be provided to HCPs at each hospital site. Training will cover delivery of the intervention including use of specific brief motivational techniques, and each HCP will also receive a training manual to support the formal training session. This training approach aims to equip HCPs with the knowledge and skills they need to conduct screening with a validated screening tool and deliver brief behavioural interventions to motivate and support patients to either reduce their drinking to low-risk levels or abstain from drinking in the perioperative period (the proposed objective for a definitive RCT).

**Table 2 Tab2:** TIDieR description of intervention

Item	Details	Page
Name	Preoperative Behavioural Intervention to Reduce Drinking before elective orthopaedic Surgery (PRE-OP BIRDS)	1
Why	Preoperative alcohol consumption is related to increased risk of postoperative complications. The aim of the intervention is to support patients to reduce or cease alcohol consumption prior to elective orthopaedic surgery.	7–11
What	Materials: Healthcare professionals (HCPs) are trained to screen for increased risk alcohol consumption and to deliver the following intervention materials:	14
	• Brief Advice Sheet • Brief Intervention Sheet • Patient Information Leaflet	17–19

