### Comparator

Patients allocated to TAU will not receive the intervention but will complete study baseline measures. As part of the feasibility study, focus groups (*N* = 3) were conducted with HCPs (total *N* = 19) from across the three hospital sites to characterise TAU. As part of the pre-assessment, all patients are asked about their alcohol consumption. Questions cover whether the patient consumes alcohol and, if so, aim to establish the number of units consumed each week. Patients considered by the preoperative assessment clinic nurse to be ‘heavy drinkers’ or those identified through blood and/or liver function tests are routinely referred to the consultant anaesthetist for anaesthetic review to ensure patient safety during anaesthesia.

Additionally, there is specialist support available for patients to reduce or cease alcohol consumption at all three participating centres. However, findings from the focus groups identified that in the preoperative assessment setting there is currently no standard process for identifying and referring patients to these services with identification being left to the judgement of the individual HCP. Further to this, referrals to these services from preoperative assessment HCPs were very low as a result of a lack of knowledge regarding how to refer patients to these services and, at one site, a requirement to ask patients if they wished to receive further support an offer which staff reported patients consistently declined. While leaflets about alcohol consumption were visibly available in the waiting areas of the preoperative assessment clinics, HCPs did not report routinely providing these to patients. In addition, these are hospital-wide services, not specific to the pre-assessment department and information or advice is not delivered by preoperative assessment clinic staff.

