Three key factors which restricted initial recruitment were identified and addressed during the feasibility work. Firstly, a number of patients demonstrated adverse responses to the term ‘risky drinking’ which previously appeared in the study title and documentation, this was amended so that wording focuses on the benefits of reducing alcohol consumption. Secondly, screening reactivity resulted in reductions in reported alcohol consumption at baseline, prior to confirmation in eligibility and meant that the number of patients who screened eligible, consented to the study, but did not go on to receive the intervention was higher than anticipated. For this reason eligibility for the RCT will be based on the initial screening score with later measures employed to track changes in alcohol consumption over the study period. Finally, allowing the patient too long to consider involvement in the study before obtaining ongoing expression of interest hindered the facilitation and organisation of intervention sessions, especially when patients were not contactable on the first attempt, and led to many patients forgetting about the study. Allowing patients a minimum of 24 h to consider their involvement means that the study information is fresh in their minds and facilitates effective coordination of preoperative assessment and intervention delivery. Further operational issues, specifically the availability of physical space and staff time in the clinics, were also identified but could not be fully addressed within the scope of this study as this would require a significant increase in financial and human resources. Further to this, obtaining research participation without an impact on patient care could be difficult if there is a temporary reduction in staff levels through sickness or absence, something which cannot be controlled. However, the pilot RCT implemented some strategies to reduce the impact of these issues. The burden on staff time and need for physical space to conduct study activities were reduced as much as possible by having research-specific activities (e.g. consent, randomisation 6-month follow-up) conducted by research rather than clinical staff and allowing screening and follow-up measures to be collected over the telephone rather than in person. In addition a ‘coping planning’ element was included in the revised HCP training and training manual. This provided specific examples of difficulties encountered during the feasibility trial and encouraged HCPs to pre-plan methods of coping should they encounter these difficulties (e.g. being short on time) as well as providing suggested coping methods if they could not come up with their own. The ongoing impact and potential mechanisms for overcoming these difficulties will be considered in the qualitative interviews with HCPs.

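### Baseline questionnaires follow open randomisation, in the intervention arm with the HCP about to give the alcohol advice, so baseline AUDIT in particular can differ by arm

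*Protocol article*

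**What the plan says.** The order has to be read from three sections of the protocol article.

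- **Screening, consent and randomisation.** At the preoperative assessment clinic, "a member of the research team (not involved in screening or delivering the intervention) will initially see the patient". That person takes consent, and then: "Once consent has been obtained, the researcher will access the Newcastle Clinical Trials Unit (NCTU) secure web-based randomisation system". The section ends: "This trial is not blinded".
- **Intervention.** "Following preoperative assessment, the patient and HCP will complete the baseline assessments shown in Table 3". These are the full AUDIT, EQ-5D and WOMAC. In the same sentence, "the HCP will then deliver the first intervention session".
- **Comparator.** "Patients allocated to TAU will not receive the intervention but will complete study baseline measures". These patients are described by their allocated arm when they complete baseline, and the section does not say who completes it with them.

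Table 3 puts consent, randomisation, baseline and the first intervention session all at Visit 1, with no order inside the visit. Under Participants—healthcare professionals, clinic HCPs generally "will receive training on study procedures, screening patients using the AUDIT C tool and completion of study baseline measures", while only a subset is trained to deliver the intervention.

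**The concern.** A baseline measure should be fixed before the patient or the assessor can know the arm. Here a patient in the intervention arm may report drinking knowing that alcohol advice comes next, to the person who will give it. A TAU patient reports knowing that no advice follows, possibly to a different kind of assessor. The baseline is then a post-randomisation measure taken under conditions that can differ by arm.

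Three things depend on it:

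- The Measures section takes changes in AUDIT, EQ-5D and WOMAC from this baseline.
- The Statistical analysis section reports completeness of the baseline measures. A patient who leaves after learning the arm but before the questionnaires has no baseline, so completion can also depend on allocation.
- The pilot rehearses the procedure for a definitive trial whose primary outcome would be drinking status around surgery. There, a baseline open to influence by allocation would matter most.

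**Working it through.** **1. Order of events.** Setting the sections side by side:

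| Step | Who | Section |
|---|---|---|
| Consent | Researcher outside screening and intervention | Screening, consent and randomisation |
| Web randomisation, unblinded | Same researcher | Screening, consent and randomisation |
| Preoperative assessment | Clinic | Intervention |
| Baseline AUDIT, EQ-5D, WOMAC | Patient with HCP (TAU assessor not named) | Intervention; Comparator |
| First intervention session | That HCP, intervention arm only | Intervention |

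No section puts baseline before randomisation or withholds the allocation until baseline is recorded.

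**2. The plan's own sample size.** It is not in dispute and reproduces. With 30 per arm needed at 6 months and 25% loss, 30 / (1 − 0.25) = 40 per arm, or 80 in total, and 80 × 0.75 = 60 retained. Reordering the visit changes none of these numbers.

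**3. What a shift would do.** The documents give no size, so the inputs here are assumptions. Let knowledge of allocation move mean reported baseline AUDIT by *b* SD in one arm, and let ρ be the baseline to follow-up correlation.

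- Error in the between-arm difference in change = *b*.
- Error in a baseline-adjusted difference ≈ ρ × *b*, with equal SDs at the two times. The pilot plans no such adjustment; this line is relevant only to a later trial.

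| *b* (SD) | Change | Adjusted, ρ = 0.5 | Adjusted, ρ = 0.7 |
|---|---|---|---|
| 0.1 | 0.10 | 0.05 | 0.07 |
| 0.2 | 0.20 | 0.10 | 0.14 |
| 0.3 | 0.30 | 0.15 | 0.21 |

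The direction is not known. Under-reporting at baseline in the intervention arm would make its later reduction look smaller; over-reporting would make it look larger.

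**4. Could the pilot see it?** The standard error of a between-arm difference in means is √(2/n) SD. With 40 per arm at baseline it is √(2/40) = 0.22 SD; with 30 per arm it is √(2/30) = 0.26 SD. A shift of 0.1 to 0.3 SD could not be told reliably from chance imbalance, so the data would not settle afterwards whether it had happened.

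**The case against.** **Little in this pilot depends on baseline.** The primary outcomes are numbers screened, recruitment and 6-month retention, and the analysis is descriptive. This stands: no effect test is invalidated, and a reader who infers a must-fix fault goes further than the documents allow.

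**The feasibility finding is not an arm effect.** The Discussion reports that "screening reactivity resulted in reductions in reported alcohol consumption at baseline". It is tempting to read this as evidence of bias by arm. But that study had no randomisation and the fall followed screening, which in this trial comes before allocation in both arms. Taking baseline earlier in the visit would not remove it. The finding shows only that self-reported drinking is easily moved.

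**A pre-randomisation drinking measure exists.** Every participant has a screening AUDIT C, on which eligibility rests. This stands, and it rules out calling baseline comparability uninterpretable. It does not fully replace a pre-randomisation full AUDIT, which is the reference for change, and it says nothing on EQ-5D or WOMAC.

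**There is little reason for EQ-5D or WOMAC to move.** Allocation to alcohol advice has no evident route to reported joint function. This mostly stands, so the concern is chiefly about AUDIT.

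**The order and the arm difference are partly inferred.** Table 3 gives no order within the visit, Fig. 1 is not shown, the protocol does not say when the patient learns the allocation, and HCPs may complete baseline in both arms. This limits certainty. Still, the three sections most naturally read as baseline after allocation, and nothing in them says otherwise.

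**The Background's 29% rise in complications per AUDIT point.** A reader might use it to argue that a small reporting shift matters clinically. It is an association between AUDIT score and complications in men having joint arthroplasty, and it has no bearing on misreporting at baseline.

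**Conclusion.** The point holds as a moderate design weakness. As written, baseline is completed after open allocation, and in the intervention arm with the HCP about to give the alcohol advice. The documents show a risk of arm-dependent reporting, mainly on AUDIT, and not its occurrence; its size and direction are unknown. The figures of 0.10 to 0.30 SD for change and 0.05 to 0.21 SD after adjustment rest wholly on an assumed shift of 0.1 to 0.3 SD and ρ of 0.5 to 0.7.

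Exposed are the descriptive changes from baseline, baseline completion by arm, and the procedure a definitive trial would inherit. Recruitment, retention and the sample size are not affected. The reason to act now is that a full AUDIT taken before randomisation cannot be recovered later, and obtaining it costs little.

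**What to change.** In Screening, consent and randomisation, in Intervention, in Comparator and in Table 3, state one order for both arms:

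1. The researcher takes consent.
2. The same researcher, who has no part in screening or intervention, offers the baseline questionnaires: AUDIT at minimum, preferably EQ-5D and WOMAC too.
3. The researcher then opens the randomisation system.
4. The completed AUDIT goes to the HCP, so that it is at hand for the intervention session.

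Record each missing or partial baseline with its reason, but do not make completion a condition of randomisation. A mandatory gate would force completion to 100% among randomised patients and empty the baseline-completion outcome that the pilot is meant to report. Also compare screening AUDIT C by arm as a descriptive check.

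The cost is some questionnaire time moved ahead of the preoperative assessment, in clinics where the Discussion says space and staff time are short. It needs no extra visit, staff or patients, and it fits the protocol's stated move of research tasks from clinical to research staff.

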### Comparator

Patients allocated to TAU will not receive the intervention but will complete study baseline measures. As part of the feasibility study, focus groups (*N* = 3) were conducted with HCPs (total *N* = 19) from across the three hospital sites to characterise TAU. As part of the pre-assessment, all patients are asked about their alcohol consumption. Questions cover whether the patient consumes alcohol and, if so, aim to establish the number of units consumed each week. Patients considered by the preoperative assessment clinic nurse to be ‘heavy drinkers’ or those identified through blood and/or liver function tests are routinely referred to the consultant anaesthetist for anaesthetic review to ensure patient safety during anaesthesia.

Additionally, there is specialist support available for patients to reduce or cease alcohol consumption at all three participating centres. However, findings from the focus groups identified that in the preoperative assessment setting there is currently no standard process for identifying and referring patients to these services with identification being left to the judgement of the individual HCP. Further to this, referrals to these services from preoperative assessment HCPs were very low as a result of a lack of knowledge regarding how to refer patients to these services and, at one site, a requirement to ask patients if they wished to receive further support an offer which staff reported patients consistently declined. While leaflets about alcohol consumption were visibly available in the waiting areas of the preoperative assessment clinics, HCPs did not report routinely providing these to patients. In addition, these are hospital-wide services, not specific to the pre-assessment department and information or advice is not delivered by preoperative assessment clinic staff.

